## Background

### Literature search and review

In preparation for this study, a systemised review of the literature was performed on preoperative and postoperative falls.^3^ This review showed that a limited number of studies on postoperative falls have been conducted, and the few that have been performed mostly study orthopaedic and elderly populations. While one study characterised postoperative falls in all surgery types, it was limited by its retrospective design, inpatient time period and exclusively male population.^4^ Another study suggested that most postoperative falls may be surgery related, especially in the first weeks following surgery. However, it only tracked falls that resulted in hospital care, and its follow-up period was limited to 90 days.^5^

Regarding the second aim of predicting postoperative outcomes, our systemised review identified just one paper that studied the association between preoperative falls and postoperative complications and readmission.^6^ However, the sample size was small (235), and the population included only men over 65 undergoing cardiac or colorectal surgery at a Veterans Affairs hospital. Using Medical Subject Heading (MeSH) terms of ‘accidental falls’, ‘postoperative period’ and each outcome, a thorough PubMed search was also performed to identify other relevant papers linking falls, surgery and each outcome of interest. This search showed that in non-surgical patients, falls are associated with greater functional dependence.^7^
^8^ In addition, preoperative frailty and geriatric syndromes, which are linked to falls, are associated with postoperative complications^9–14^ and readmission.^15^
^16^ Together, these findings suggest that falls before surgery may presage worse surgical outcomes. However, replication in a larger study is needed.

An additional literature search was performed to identify important confounders for each proposed outcome. Searches consisted of PubMed MeSH for each outcome, along with the MeSH, ‘Risk Factors’, in order to generate a thorough search. Variables that were strongly associated with the outcomes and that would be available to clinicians during preoperative assessment were included as confounders. In addition to confounders from the literature, our previous study on preoperative falls^17^ guided selection of confounders for postoperative falls. That is, variables with ORs of 1.5 or higher were included.

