Table 1 contains all variables to be collected for the study, along with the form of the variable, its source, time point for collection and whether or not it comes from a standardised tool. Of note, the informaticist performs rigorous data validation on each queried variable. If continuous variables are found to exhibit non-linearity, they will be categorised in accordance with their distribution.

**Table 1 BMJOPEN2016011570TB1:** Characteristics of all variables used in this study

Type	Variable name	Form	Source	Time	Use of standardised tool
Explanatory	Preoperative falls	0, 1, 2, 3+	Survey	BL	Yes^21^
	Charlson Comorbidity Index	Ordinal, 0–12	CPAP H&P	BL	Yes^29^
	ASA physical status	Ordinal, 1–6	Anaesthesia record	Surgery	Yes^30^
	Procedural cardiac risk	Ordinal, 5 categories from high to low	CPAP clinician	BL	Yes^31^
Outcome	Postoperative falls	Binary (V.2); 0, 1, 2, 3+ (V.3)	Survey	30 days, 1 year	Yes^21^
	Functional dependence	Ordinal, 0–100 by 5	Survey	30 days, 1 year	Yes^32^
	Physical quality of life	Continuous, 0–100	Survey	30 days, 1 year	Yes^33^ ^34^
	Mental quality of life	Continuous, 0–100	Survey	30 days, 1 year	Yes^33^ ^34^
	In-hospital complications	Dichotomous	Survey	30 days	No
	Readmission	Dichotomous	Survey	30 days	No
Demographic	Age	Continuous	Medical record	BL	NA
	Sex	Dichotomous	Medical record	BL	NA
	Race	Nominal	Medical record (patient report)	BL	NA
	Ethnicity	Hispanic/Latino or not	Medical record (patient report)	BL	NA
	Body mass index	Continuous	CPAP nurse	BL	Yes
Confounder	Functional dependence	Ordinal, 0–100 by 5	CPAP nurse	BL	Yes^32^
	Physical quality of life	Continuous, 0–100	Survey	BL	Yes^33^ ^34^
	Mental quality of life	Continuous, 0–100	Survey	BL	Yes^33^ ^34^
	Smoking status	Current, past, never	CPAP physician or nurse	BL	NA
	Physical activity level	<4, 4–6, 6–10, >10 (METs)	CPAP physician	BL	Yes^35^
	Incontinence	Dichotomous (any issue)	CPAP nurse	BL	Yes^32^
	Toileting difficulty	Dichotomous (any issue)	CPAP nurse	BL	Yes^32^
	Mobility issue	Dichotomous (any issue)	CPAP nurse	BL	Yes^32^
	Neurological impairment (stroke, paraplegia or quadriplegia, Parkinson disease or multiple sclerosis)	Dichotomous	CPAP H&P	BL	No
	Chronic pain	Dichotomous	CPAP physician ROS	BL	No
	Dizziness/vertigo	Dichotomous	CPAP physician ROS	BL	No
	Depression	Dichotomous	CPAP H&P	BL	No
	Anxiety	Dichotomous	CPAP H&P	BL	No
Descriptive	Fall-related injury	Check all that apply	Survey	BL, 30 days, 1 year	No

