Aim 2 explores whether a preoperative history of falls serves as a useful tool for predicting surgical outcomes. First, we will calculate a crude dose–response relationship between the number of falls at baseline (0, 1, 2, 3+) and each outcome (postoperative falls, postoperative functional dependence, postoperative quality of life, in-hospital complications and 30-day readmission). For comparison, we will also calculate the crude dose–response relationship for a falls and injuries composite scale.^27^ We will examine the bivariate relationship between preoperative falls and each complication subcategory (heart/stroke, lung, blood clots, kidney/intestine, nerve injury, infection, delirium or other) using χ^2^ tests for the purpose of hypothesis generation.

To assess the relationship after controlling for important confounders, we will use logistic regression (categorical outcomes) and linear regression (continuous outcomes). Specifically, we will use forced entry of all prespecified variables. We will check all models for linearity of logit, multicollinearity, influential cases, conformity to linear gradients and goodness of fit. Since the number of possible interaction terms is large (between 45 and 91 per model), including all of them creates an unacceptably large risk of type I error. Therefore, our statistical consultant ([name]) recommended selecting only 10% of the most clinically relevant interaction terms. Using a combination of prior research and clinical judgement, two investigators ([name] and [name]) selected the 10% most clinically relevant interaction terms for each model. The online supplementary material contains these prespecified interaction terms. Non-significant interaction terms (p>0.01) will be removed from the model.

10.1136/bmjopen-2016-011570.supp8Supplementary data

Each model will include the following demographic and explanatory variables: age, sex, race (white vs non-white), BMI, preoperative falls history (0, 1, 2, 3+), Charlson Comorbidity Index (≥3 vs <3), American Society of Anesthesiology (ASA) physical status (≥3 vs <3) and procedural cardiac risk. On the basis of a careful literature search of each outcome variable (see the Literature search and review section), we selected confounding variables that are both routinely collected and known at the time of surgery planning. Outcome variables and their corresponding outcome-specific confounders are listed below.

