Presence or absence of at least one fall in the 30 days (primary outcome) and 1 year following surgery:
Physical activity level (<4 vs >4 metabolic equivalents (METs));Baseline altered elimination (bowel or bladder);Baseline mobility abnormality;Dizziness/vertigo;Depression.▸Barthel Index that is worse than baseline, at 30 days and 1 year after surgery:
Baseline Barthel Index score;Neurological impairment;Mood disorder (depression or anxiety);Smoking status.▸Physical quality of life score, at 30 days and 1 year after surgery:
Baseline physical quality of life score;Preoperative physical activity level (<4 vs >4 METs);Chronic pain;Mood disorder (depression or anxiety);Smoking status.▸Mental quality of life score, at 30 days and 1 year after surgery:
Baseline mental quality of life score;Chronic pain;Mood disorder (depression or anxiety).▸Presence or absence of any complication that occurred in the hospital, as reported in the 30-day survey:
Smoking status.▸Presence or absence of readmission at 30 days, as reported in the 30-day survey:
In-hospital complications (30-day survey);Incontinence.

After running each model, we will substitute the number of falls (0, 1, 2, 3+) explanatory variable for the falls and fall injuries composite scale^27^ to evaluate which scale better predicts outcomes. Since we test multiple hypotheses, the threshold for significance will be α=0.01. We will report results using ORs and 99% CIs, along with variance estimates for regression parameters.

Using SAS/STAT software, V.9.4 (SAS Institute, Cary, North Carolina, USA), [name] will perform all analyses. Analysis will begin only after acceptance of this protocol for publication. This approach reassures readers that key analyses were truly prespecified rather than post hoc. If the authors decide to perform post hoc analyses, these will be described as such and will be performed for the purpose of further hypothesis generation.

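### The complications model, and to a lesser degree the readmission model, is open to residual confounding by baseline function and activity that the study already records

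*Protocol article*

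**What the plan says.** In the literature review the protocol article states that "preoperative frailty and geriatric syndromes, which are linked to falls, are associated with postoperative complications"; the same sentence goes on to name readmission. It then gives its selection rule: "Variables that were strongly associated with the outcomes and that would be available to clinicians during preoperative assessment were included as confounders".

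Table 1 lists, under the type Confounder and measured at baseline, functional dependence ("Ordinal, 0–100 by 5"), physical activity ("<4, 4–6, 6–10, >10 (METs"), mobility, toileting difficulty and incontinence.

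The Analysis section says the regression models are there to control for important confounders. Every model carries age, sex, race, BMI, fall history, Charlson and ASA (each cut at 3) and procedural cardiac risk. The outcome-specific additions are then:

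- complications: "Presence or absence of any complication that occurred in the hospital, as reported in the 30-day survey: Smoking status";
- readmission: "In-hospital complications (30-day survey);Incontinence";
- postoperative falls: METs, elimination, mobility, dizziness and depression;
- functional decline: baseline Barthel, neurological impairment, mood disorder and smoking;
- physical quality of life: METs among others.

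The Limitations section explains absent confounders by what the database holds.

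**The concern.** By the protocol's own account, frailty is related to the exposure and to both outcomes. No frailty instrument is listed, but function, mobility and activity are recorded and are treated as confounders elsewhere in the same plan. The complications model has no functional item at all. The readmission model has one, incontinence, which Table 1 takes from the same standardised tool as functional dependence. Lack of data cannot explain leaving out variables that sit in Table 1 and enter the sibling models, and no other specific reason is given.

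At stake is the reading of Aim 2c. The Justification section looks ahead to fall history improving preoperative decisions. If fallers are also the less active and more dependent patients, part of the fall-history OR may reflect what the clinic's functional assessment already shows, and these two models cannot separate the two.

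**Working it through.** **1. The plan's own figures.** Inputs from Sample size calculations: N = 7800, 26% fallers, 28% complications, 5.5% readmission, 80% power, two-sided α = 0.05. A two-proportion calculation gives these detectable increases, taking the stated rate first as the non-faller rate and then as the overall rate:

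- complications: 11.8% and 12.0% (stated: 12%);
- readmission: 31.7% and 33.2% (stated: 34%; with continuity correction and 5.5% as the overall rate, a 34% increase needs N = 7776).

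Both stated figures reproduce. At the analysis threshold of α = 0.01 they become 14–15% and 39–41%.

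**2. Is there room for more terms?** Events are 0.28 × 7800 = 2184 and 0.055 × 7800 = 429.

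- Complications: 8 + 1 = 9 variables, 2184/9 = 243 events per variable; with two more, 2184/11 = 199.
- Readmission: 8 + 2 = 10 variables, 429/10 = 43; with two more, 429/12 = 36.
- Counting parameters for readmission (falls 3, procedural risk 4, eight single terms) gives 15. Adding Barthel (1) and four-category METs (3) gives 19, and 429/19 = 23.

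The protocol's rule is 10 per predictor. Sample size is no reason for the omission.

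**3. Crude size of the bias (assumed values; none are in the documents).** For an omitted binary factor with prevalence p1 in fallers, p0 in non-fallers and outcome risk ratio g, the spurious risk ratio is [1 + p1(g − 1)] / [1 + p0(g − 1)].

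- p0 = 0.10, p1 = 0.20, g = 1.5: 1.10/1.05 = 1.05.
- p0 = 0.20, p1 = 0.40, g = 3: 1.80/1.40 = 1.29.

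This ignores everything already in the models.

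**4. Size after partial adjustment (simulation, 400,000 records, assumed values).** Low function has 20% prevalence and is correlated with age, ASA and Charlson. Its OR with falling is 1.5 or 2.0 and with the outcome 1.5, 2.0 or 2.5. Falls have no true effect. All fits adjust for age, ASA and Charlson.

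| Outcome | Fall OR without function | Fall OR with function |
|---|---|---|
| Complications | 1.04 to 1.12 | 0.98 to 1.01 |
| Readmission | 1.02 to 1.13 | 0.99 to 1.04 |

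The departures from 1.00 in the last column are simulation noise. Taking the ratio of the two ORs in each scenario removes noise common to both fits: 1.039/1.010 = 1.03 up to 1.117/1.001 = 1.12 for complications, and 1.020/0.988 = 1.03 up to 1.134/0.999 = 1.14 for readmission. The readmission fits do not include incontinence, and neither set includes procedural risk, so the real residual could be smaller.

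**5. Consequence at α = 0.01 (crude two-proportion calculation, no true effect).**

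- Complications: a spurious risk ratio of 1.05 is declared significant about 9% of the time, and one of 1.09 about 34%. On the OR scale these are (0.294/0.706)/(0.28/0.72) = 1.07 and (0.3052/0.6948)/(0.28/0.72) = 1.13. The first lies inside the simulated range and the second just above it.
- Readmission: risk ratios of 1.09 and 1.13 give about 4% and 9%.

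**The case against.** - **The aim is prediction.** Aim 2c asks whether fall history predicts these outcomes, and frailty is cited as the reason it might. For pure prediction an association that runs through frailty is legitimate. That stands for a crude or lightly adjusted OR, but the Analysis section says these models control for important confounders, and sibling models adjust for function or activity under the same aim.
- **Over-adjustment.** The falls occurred in the six months before surgery, while Barthel, mobility and METs are recorded at the baseline visit. Low function may partly result from a fall or measure the same thing. This stands, and is why both ORs should be shown rather than one replaced.
- **The selection rule is not shown to be broken.** The protocol says frailty is associated with the outcomes; it does not say that Barthel or METs are strongly associated with them, and the searches were done per outcome. This stands as far as it goes: treating these variables as markers of frailty is an inference, though one supported by the protocol's own use of them elsewhere.
- **The crude association is already planned.** True, but it is not the fully adjusted OR against which a functional block would be compared.
- **The likely bias is below the 20% minimum important difference.** Correct for the simulated range. It can still affect significance for complications.

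A reader might infer that function is recorded for every patient. Table 1 shows only that it is collected, and the plan expects missing data. Nor is neurological impairment an equally ready addition: the Limitations section calls its completeness unknown.

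**Conclusion.** The concern holds as residual confounding. The complications model has no measure of function or activity. The readmission model has one functional item and is less exposed. The inconsistency with the literature review, Table 1 and the sibling models is plain from the text.

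The size is not. The spurious OR of roughly 1.02 to 1.13 rests wholly on assumed prevalences and effects, and only age, ASA and Charlson were adjusted for. It matters mainly for complications, where the study is sensitive to small effects. For readmission it is small against a detectable increase of 34%.

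A reader might go further and conclude that the comparison is confounded by a known amount, or take the crude 1.05 to 1.29 as the expected error. The documents support neither: they give no prevalence or effect for low function, and the crude figures ignore variables that are in every model. Both outcomes are secondary, so the primary falls result, whose model already includes METs and mobility, is not touched.

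**What to change.** Keep the listed complications and readmission models. Prespecify for each a second forced-entry step that adds METs and either the baseline Barthel Index or mobility, with the choice fixed before analysis. In the readmission model Barthel overlaps with incontinence, which the planned multicollinearity check would cover. Handle missing values by the multiple imputation already planned. Report the fall-history OR with its 99% CI before and after this step, and base any statement that fall history adds to existing preoperative assessment on the second OR. Amend the Limitations sentence on availability, since it does not explain these two models.

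The cost is a few lines of protocol text and a few degrees of freedom; no new data item is needed. The second OR may be smaller and may be over-adjusted, so it should be read beside the first. The change belongs before the data are analysed, because the protocol labels later additions post hoc.

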## Specific aims

*Aim 1*: Describe characteristics of postoperative falls in an unselected surgical population, including their rate, timing, associated injuries and risk factors.

We hypothesise that the occurrence, injuries and risk factors of postoperative falls will be similar to those of preoperative falls, and the rate of postoperative falls will decline from 30-days after surgery to 1 year after surgery.

*Aim 2a*: Determine whether a preoperative history of falls serves as a useful tool for predicting falls in the 30 days (primary outcome) and 1 year following surgery of all types.

*Aim 2b*: Determine whether a preoperative history of falls predicts patient-centred outcomes including functionality and quality of life at 30 days and 1 year after surgery (secondary outcomes).

*Aim 2c*: Replicate findings that a preoperative history of falls predicts in-hospital surgical complications and readmission at 30 days (secondary outcomes).

We hypothesise that a history of preoperative falls will predict poor postsurgical outcomes, including postoperative falls, functional dependence, poor quality of life, in-hospital complications and readmission.

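### The readmission model adjusts for in-hospital complications, a postoperative outcome that breaks the protocol's own preoperative rule for confounders, so its falls OR does not answer the readmission part of Aim 2c

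*Protocol article*

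**What the plan says.** The Analysis section gives every model eight common variables: age, sex, race, BMI, preoperative falls history, Charlson index, ASA status and procedural cardiac risk. It then adds outcome-specific confounders. For readmission these are "In-hospital complications (30-day survey);Incontinence". Entry is not data-driven: "we will use forced entry of all prespecified variables".

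The selection rule appears twice. In Analysis: "we selected confounding variables that are both routinely collected and known at the time of surgery planning". In Literature search and review, variables strongly associated with the outcome that "would be available to clinicians during preoperative assessment were included as confounders".

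Table 1 (Data to be collected) has a row reading "In-hospital complications Dichotomous Survey 30 days No". It stands in the outcome block, not the confounder block.

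Under Specific aims, Aim 2c is to "Replicate findings that a preoperative history of falls predicts in-hospital surgical complications and readmission at 30 days (secondary outcomes", and the overall hypothesis is that "a history of preoperative falls will predict poor postsurgical outcomes, including postoperative falls, functional dependence, poor quality of life, in-hospital complications and readmission".

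The Sample size calculations section states that the results of interest are the regression ORs, not the crude bivariate comparisons.

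**The concern.** A covariate that arises after the exposure, before or alongside the outcome, and that the study expects the exposure to predict, does not act as a confounder. Conditioning on it takes out of the falls coefficient any association with readmission that passes through complications.

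The model also stops answering the question asked. Aim 2 asks whether a falls history is a useful predictor for preoperative decision-making. An OR that holds complication status fixed describes patients whose postoperative course is already known.

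If much of the association runs through complications, the readmission result could look weak and be published as a failed replication, when the weakness came from the choice of covariate.

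**Working it through.** **1. The passages side by side**

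| Item | Protocol article | Status of in-hospital complications |
|---|---|---|
| Rule for confounders | Analysis; Literature search and review | Must be known before surgery: not met |
| Source and time | Table 1 | Patient survey at 30 days |
| Type | Table 1 | Outcome |
| Place in the hypothesis | Specific aims, Aim 2c | Predicted by falls history, as is readmission |
| Place in the readmission model | Analysis | Forced-entry covariate |

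All other covariates in the listed models are baseline, demographic or surgery-day variables. This is the only one taken from a follow-up survey. The one planned readmission analysis without it is the crude dose–response by number of falls, which has no confounder control. The Limitations section does not mention the issue.

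**2. The protocol's detectable effect for readmission**

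Inputs from Sample size calculations: N = 7800, 26% exposed, 5.5% readmitted, two-sided α = 0.05, detectable increase 34%.

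- Groups: 7800 × 0.74 = 5772 unexposed; 7800 × 0.26 = 2028 exposed.
- Reading 5.5% as the overall rate: p0 = 0.055 / (0.74 + 0.26 × 1.34) = 0.0505; p1 = 1.34 × 0.0505 = 0.0677.
- Power = Φ[(p1 − p0 − 1.96·SE0)/SE1], with SE0 the pooled and SE1 the unpooled standard error. Here SE0 = 0.00589 and SE1 = 0.00628.
- (0.01718 − 1.96 × 0.00589)/0.00628 ≈ 0.90, so power is 81.6%.

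The stated figure reproduces. It is for the crude falls–readmission contrast, not for an OR conditional on complications. On the odds scale, 34% corresponds to OR = (0.0677/0.9323)/(0.0505/0.9495) = 1.365, log OR 0.311.

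**3. What conditioning removes**

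The documents give neither the falls–complication nor the complication–readmission association. Two things are therefore assumed: a complication–readmission OR (M) of 2 to 5, and a relative increase in complications among fallers (R). The value R = 1.12 is the protocol's own detectable increase for complications; R = 1.5 is a larger illustration. No other confounding is modelled.

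- Complication rates, with 28% overall: m0 = 0.28/(0.74 + 0.26R), m1 = R·m0. R = 1.12 gives 27.2% and 30.4%; R = 1.5 gives 24.8% and 37.2%.
- Solve for b: (1 − m0)·expit(b) + m0·expit(b + ln M) = p0.
- Solve for d, the complication-adjusted log OR for falls: (1 − m1)·expit(b + d) + m1·expit(b + d + ln M) = p1.
- Share removed = 1 − d/0.311.

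| Falls raise complications by | M | Adjusted falls OR | Log OR removed |
|---|---|---|---|
| 0% | 2 to 5 | 1.37 to 1.38 | none |
| 12% | 2 | 1.33 | 7% |
| 12% | 5 | 1.30 | 16% |
| 50% | 2 | 1.24 | 30% |
| 50% | 5 | 1.10 | 70% |

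For example, with R = 1.5 and M = 5: b = −3.584, d = 0.093, and 1 − 0.093/0.311 = 70%.

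**4. Effect on power**

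Wald power at α = 0.05, with no other covariates, is 83% for the total OR of 1.365. With the complication term it is 77% to 67% if R = 1.12, and 52% to 13% if R = 1.5, as M goes from 2 to 5.

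**The case against.** The protocol says that falls *predict* complications, not that they cause them, and its background links falls with frailty and geriatric syndromes. Falls may be only a marker, so calling complications an established mediator goes beyond the text. That is fair, and the point does not need it. The breach of the protocol's own preoperative rule stands under a purely predictive reading, because the model still conditions on information unavailable before surgery.

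The covariate is openly prespecified, and a falls OR conditional on complications can be interpreted if it is labelled as such. The plan does not label it so: the variable appears in a list of confounders, and the regression OR is named as the result of interest.

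The crude dose–response analysis leaves the term out. This mitigates only in part, because that analysis controls for nothing.

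A reader might also infer that Aim 2c as a whole cannot be answered. The documents do not support that: the complications half of the aim has its own model, whose only outcome-specific covariate is smoking status. The primary outcome model is likewise free of the problem.

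**Conclusion.** The point holds for one covariate in one secondary-outcome model. The readmission model contradicts the protocol's stated rule for confounders, and its falls OR does not answer the readmission part of Aim 2c. It should be fixed, but it does not threaten the primary result.

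The size of the loss is an assumption-dependent range that starts at zero. It is nil if falls are unrelated to complications, about 7–16% of the log OR if falls raise complications by 12%, and 30–70% if by 50%. These figures assume complication–readmission ORs of 2 to 5 and a total 34% increase in readmission.

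Three stronger readings are tempting and not supported:

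- **That more than half of the effect disappears.** This depends on the inputs. Take a direct OR of 1.15, with falls–complication and complication–readmission ORs of 1.5 and 4, 1.5 and 6, or 1.3 and 4. The total ORs are 1.31, 1.35 and 1.25, and 48%, 54% and 37% of the log OR is removed. Only one of the three exceeds half.
- **That the estimate drops below the protocol's 20% minimum important difference.** Assuming a direct OR of 1.15 builds that in. In the table under the check, the adjusted OR lies on either side of 1.20 depending on the assumptions.
- **That the bias is always toward the null.** Conditioning may also add bias through unmeasured causes shared by complications and readmission, and the direction of that bias is not known.

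**What to change.** Remove in-hospital complications from the main readmission model, leaving the eight common variables and incontinence. If the association not running through complications is of interest, report the complication-adjusted model separately, labelled as an exploratory direct-effect analysis, and say that it uses postoperative information.

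The cost is one covariate deleted from one model. No new data are needed, and the protocol says analysis starts only after its acceptance, so the change can still be prespecified. Any prespecified interaction term in that model that involves complications would need to go as well; the list is in supplementary material not seen here.
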